### Data collection, primary outcome and power calculation

#### Effect evaluation

Data with regard to the effect evaluation of the SELF-program will be gathered from both nurses and geriatric clients. All data will be collected through digitalized questionnaires.

### Nurses

Since the SELF-program is directly pointed at nurses, this participant group is considered the primary target group. The primary outcome for nurses, i.e. the level of stimulation behavior of self-reliance in ADL among geriatric clients, will be assessed at baseline (before implementation of the SELF-program; T0), directly after implementation of the SELF-program (approximately 3 months after the baseline assessment; T1), and 9 months after the baseline assessment (T2). The validated self-report MAINtAIN questionnaire will be used to assess the primary outcome measure [42]. The MAINtAIN comprises three subscales with a total of 19 items, representing whether nurses stimulate clients in a variety of daily activities, that can be rated on a 9-point Likert scale, ranging from ‘never’ to ‘always’. Of the 19 items, 8 deal with encouraging ADL, 6 with encouraging instrumental ADL and 5 with encouraging general function and physical activity. The 8 items focusing on encouraging ADL will be used as a the primary outcome.

Demographic characteristics of nursing care professionals will be assessed at baseline only. These include the participants’ gender (male, female or open answer option), age, education level (low; no education up to lower technical education, medium; general secondary education up to secondary vocational education or high; school of higher general secondary education up till university degree), nursing profession (nursing aide, certified nursing assistant or registered nurse), years of working experience in nursing care and within the current care setting, and number of working hours according to contract.

### Geriatric clients

The main outcome for geriatric clients, i.e. self-reliance in daily functioning, will be assessed at baseline (before the implementation of the SELF-program for care professionals; T0), directly after implementation of the SELF-program (approximately 3 months after the baseline assessment; T1), and 6 months after the baseline (T2). The relative shorter follow-up period at T2 for geriatric clients compared to the one for nursing care professions will be applied because a higher level of turnover of geriatric clients is to be expected given the nature of the setting. The Groningen Activity Restriction Scale (GARS-4) will be used to assess the perceived self-reliance in daily functioning of geriatric clients [43]. The GARS-4 consists of two subscales with a total of 18 items that can be rated through a hierarchical 4-point answering scale ranging from ‘Yes, I can do the particular task completely independently without any effort’ to ‘No, I cannot do the particular task completely independently, only with help from others’. Of the 18 items, 11 items examine self-reliance in ADL activities and 7 items examine self-reliance in instrumental ADL activities. Only the 11 items of the ADL-subscale will be assessed given the 7 items of the instrumental ADL-subscale are less applicable to geriatric clients residing in nursing homes.

Demographics of geriatric clients will be assessed at baseline only. These include the client’ gender (male, female or open answer option), age, education level (low; no education up to lower technical education, medium; general secondary education up to secondary vocational education or high; school of higher general secondary education up till university degree), living arrangement (single, married, in a relation whether or not living together, divorced, widowed), years of receiving nursing home care, and whether and from whom the client received informal care. For both their own and their client questionnaires, nurses will be prompted periodically to complete either the baseline or follow-up questionnaires in case these are yet to be completed.

### Sample size calculation

Given the cluster-randomized trial design, the guidelines prescribed by Breukelen and Candel (2012) were applied for sample size calculation (N) [44]. The SELF-program is expected to induce a difference in groups’ averages of the primary outcome (the MAINtAIN-score), corresponding to a small to medium effect size of 0.4 (Cohen’s *d*). Further, the mean cluster size, i.e. the average number of nursing care professionals per ward, is estimated to be 15. Using the two-tailed t-test, with power and significance level of 80% and 5%, respectively, the required number of clusters (K) was then computed, using an interclass correlation coefficient of 0.05 to correct for the cluster-randomized design effect (DE), yielding K ~ 8. Subsequently, K was increased in 10% to adjust for differences cluster sizes, and the associated sample size was further augmented to account for a 20% attrition of care professionals between baseline and post-treatment. This yielded a total sample size of *N* = 330 (165 per arm) care professionals and geriatric clients in K = 22 nursing home wards, or 11 ‘dyads’. In order to achieve adequate participant enrolment, we aim to include > 22 nursing home wards.

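### The stated sample-size inputs give about 11 wards per arm, not 8, so 22 wards and 330 nurses carry about 66–70% power instead of 80%

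*Protocol article*

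**What the plan says.** The section on sample size calculation in the protocol article states every input. The expected difference on the MAINtAIN score is given as "corresponding to a small to medium effect size of 0.4" and the cluster size as "the average number of nursing care professionals per ward, is estimated to be 15". The test is described by "Using the two-tailed t-test, with power and significance level of 80% and 5%, respectively". The number of clusters then follows, "using an interclass correlation coefficient of 0.05 to correct for the cluster-randomized design effect (DE), yielding K ~ 8".

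Two inflations come next: "K was increased in 10% to adjust for differences cluster sizes, and the associated sample size was further augmented to account for a 20% attrition". The attrition figure refers to nurses. The result is N = 330 (165 per arm), in 22 wards or 11 dyads. The same total is assigned to "care professionals and geriatric clients in K = 22 nursing home wards". The section closes with an aim, not quantified, to include more than 22 wards. It mentions no correlation between baseline and follow-up and no gain from pair-matching.

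**The concern.** A published list of inputs and the result said to follow from it should agree, and here they do not. The figure for K drives everything after it: the number of wards, the total of 330 and the implied 80% power for the primary outcome. If K is too small by about three wards per arm, the allowances for unequal ward sizes and attrition are absorbed in making up the shortfall and protect against nothing. The trial would then have a materially higher chance of missing the effect it was designed to find, and a reader of a null result would rely on a stated power that the design does not have.

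**Working it through.** **Inputs** (all from the sample size section): d = 0.4 with SD = 1; two-sided α = 0.05; power 80%; m = 15 nurses per ward; ICC = 0.05; +10% clusters for unequal sizes; 20% attrition; equal allocation.

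**1. The plan's own chain, starting from K = 8.** 8 × 1.10 / 0.80 = 11.0 wards per arm; 2 × 11 = 22 wards; 22 × 15 = 330 nurses. This matches the stated total exactly. So K ~ 8 is a per-arm figure, and the inflation steps are arithmetically sound. Only K itself is in question.

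**2. K from the stated inputs.**
- Individually randomised: n per arm = 2(1.960 + 0.842)² / 0.4² = 98.1 (100 with the t distribution).
- Design effect: 1 + (15 − 1) × 0.05 = 1.70.
- Clustered: 98.1 × 1.70 = 166.8 per arm.
- Wards: 166.8 / 15 = 11.1 per arm (100 × 1.70 / 15 = 11.3 with the t-based number).

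The requirement before inflation (11.1 wards, 167 nurses per arm) is therefore practically the protocol's final size after inflation (11 wards, 165 nurses per arm).

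**3. Power for d = 0.4.** Effective n per arm = K·m / [1 + (m − 1) × 0.05], divided by 1.1 where the unequal-size allowance applies. The noncentrality is d × √(effective n / 2). The t column uses 2K − 2 degrees of freedom.

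| Design per arm | Effective n | Noncentrality | Power, normal | Power, t |
|---|---|---|---|---|
| 8 wards × 15, no loss | 70.6 | 2.38 | 66% | 60% |
| 11 wards × 15, no loss | 97.1 | 2.79 | 79.6% | 75.5% |
| 11 wards × 12 (20% attrition) | 85.2 | 2.61 | 74% | 70% |
| 11 wards × 12, and the 10% size allowance | 77.4 | 2.49 | 70% | 66% |

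In the last row the effect detectable with 80% power is d = 0.45 (normal) or 0.47 (t).

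**4. The size that the protocol's method requires.** 11.12 × 1.10 / 0.80 = 15.3 wards per arm, which is 31–32 wards and about 460–480 nurses. If attrition is treated as 12 completers per ward (design effect 1 + 11 × 0.05 = 1.55) with the 10% allowance, 14 (normal) to 15 (t) wards per arm suffice: 28–30 wards, or 420–450 nurses recruited.

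**5. What would produce 8.** Changing one input at a time:
- one-sided α: 8.8 wards per arm
- ICC of about 0.016: 8
- d of about 0.47: 8
- 30 nurses per ward: 8.0
- K = 8 read as a total (4 wards per arm): power of only 39% (normal) or 29% (t)
- a variance factor of 8 / 11.12 = 0.72: 8. This means r = √(1 − 0.72) ≈ 0.53 in a baseline-adjusted analysis, or r = 1 − 0.72/2 = 0.64 in a change-score analysis.

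All but the last contradict a stated value or make matters worse. The last needs an input that the section does not give.

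**The case against.** The strongest defence is that an input was left out of the article and the arithmetic itself was right. The section says a published guideline for cluster trials was followed. The effect evaluation under data analyses plans a mixed model on repeated measurements, in which a baseline correlation would reduce the variance. A correlation of 0.5 gives 8.3 wards per arm, close to the stated value. This is plausible, but it remains an assumption: the section describes a two-tailed t-test on a difference in group averages and names no correlation. It explains how 8 might have arisen but does not make the text correct as written.

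The power figure is also conditional. The 66–70% applies both allowances and assumes no gain from baseline data. With attrition alone it is 70–74%; with neither allowance it is 75.5–79.6%. The lower end of each range uses a ward-level t-test, and the section does not say at which level its t-test operates. These conditions should be stated beside the figure. Both allowances are nevertheless the protocol's own.

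The aim of more than 22 wards could close the gap, but it has no number and is offered to secure enrolment, with no link to power.

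Finally, the trial is powered on nurses, the primary target group, so the absence of a client calculation is not an arithmetic error. It is true that the 330 clients rest on nurse-based inputs, while the section on geriatric clients expects "a higher level of turnover of geriatric clients is to be expected given the nature of the setting", but the main point does not depend on this.

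**Conclusion.** The concern holds. K ~ 8 does not follow from the stated inputs, which give 11.1 wards per arm. The final 22 wards and 330 nurses match the requirement before inflation, so they contain no reserve for unequal ward sizes or attrition. With both of those allowances at the protocol's values, power for d = 0.4 is about 66–70%. The chance of missing a true effect of that size is then 30–34%, not 20%.

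The mismatch itself is certain. The power figure rests on ICC 0.05, 12 completers per ward, a 10% efficiency loss and no variance reduction from baseline data or matching. A disclosed and justified baseline correlation of about 0.53 (adjusted analysis) or 0.64 (change score) would restore the stated K.

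**What to change.** Rewrite the sample size paragraph in one of two ways.

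1. **If a further assumption produced K ~ 8**, state it with its value and justification. For a baseline correlation, also identify the baseline-adjusted or change-score analysis it belongs to, and make that consistent with the primary treatment-by-time analysis.
2. **If there was no such assumption**, correct K to about 11 wards per arm before inflation. State that 22 wards and 330 nurses give about 66–70% power for d = 0.4 once both allowances are applied, or 80% power for d of about 0.45–0.47.

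In both cases, say what the aim of more than 22 wards is meant to achieve; on the stated inputs, 80% power needs about 28–32 wards. Add that the total of 330 carries no power claim for clients.

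The cost is a revised paragraph and, under the second option, a less favourable stated power. No additional participants are required.

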**Method:**

The proposed CRT has three objectives, including getting insight into the program’s: (1) effectiveness regarding activity stimulation behavior of nurses and self-reliance in ADL of geriatric clients, and (2) cost-effectiveness from a societal perspective including assessments of quality of life and health-care use. Measurements will take place prior to program implementation (baseline), directly after (T1), and in long-term (T2). Parallel to the CRT, a process evaluation will be conducted to provide insight into the program’s: (3) feasibility regarding implementation, mechanisms of impact and contextual factors.

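### The 80% power has no time point and its attrition allowance stops at T1 (about 3 months); the stated inputs give about 70% at T1 and 62–68% at T2 if 25–40% are lost

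*Protocol article*

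**What the plan says.** Under Sample size calculation, the protocol article plans on a difference "corresponding to a small to medium effect size of 0.4". It takes the ward size from "the average number of nursing care professionals per ward, is estimated to be 15", and sets the error rates by "Using the two-tailed t-test, with power and significance level of 80% and 5%, respectively". The number of clusters is then found "using an interclass correlation coefficient of 0.05 to correct for the cluster-randomized design effect (DE), yielding K ~ 8". Next, "K was increased in 10% to adjust for differences cluster sizes", and the sample is raised again "to account for a 20% attrition of care professionals between baseline and post-treatment". The result is 330 nurses in 22 wards, 11 per arm, with an aim to include more than 22.

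The Abstract (Method) sets out the waves: "Measurements will take place prior to program implementation (baseline), directly after (T1), and in long-term (T2". For nurses, the outcome section places T1 about 3 months after baseline, directly after the programme, and then adds a third measurement: "and 9 months after the baseline assessment (T2"). The effect analysis is a three-level mixed model with a treatment-by-time interaction. It does not name either follow-up as the primary time point.

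**The concern.** The only attrition allowance ends at about month 3 of a primary outcome that runs to month 9. The remaining interval is twice as long. Nurses consent and complete baseline before the programme, and no replacement of leavers is described. If leavers do not return, cumulative loss at T2 cannot be below loss at T1. Yet 80% power is stated once, for the primary outcome, with no time point.

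The design promises a long-term answer. A reader who takes 80% as the power of the trial may read a null T2 result as evidence that the effect does not last. That reading needs a T2 power that the article does not give. It also needs the 80% to be right at T1, which has to be checked first.

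**Working it through.** **Inputs.** All come from Sample size calculation: two-sided 5%, power 80%, d = 0.4 (SD 1), ward size m = 15, ICC = 0.05, 10% for unequal ward sizes, 20% attrition to post-treatment, 11 wards per arm. Attrition to 9 months is not in the document; 25%, 30% and 40% total loss are assumed values.

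**1. The plan's own chain.** 8 × 1.10 / 0.80 = 11 wards per arm, so 22 wards, and 22 × 15 = 330 nurses. The chain is correct arithmetic and works only if 8 is a number per arm.

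**2. Does 8 per arm follow from the inputs?**
- Unclustered n per arm = 2 × (1.960 + 0.842)² / 0.4² = 98.1.
- Design effect = 1 + (15 − 1) × 0.05 = 1.70.
- Wards per arm = 98.1 × 1.70 / 15 = 11.1.

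It does not. The inputs need 11.1 wards per arm before any inflation. With 8 wards of 15 per arm, effective n per arm is 120 / 1.70 = 70.6, and power is Φ(0.4 × √(70.6/2) − 1.96) = 66%. The planned 330 is therefore close to the uninflated requirement (2 × 98.1 × 1.70 = 334). The plan's own inflation applied to 11.1 gives 11.1 × 1.10 / 0.80 = 15.3, so 16 per arm: 32 wards and 480 nurses.

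**3. Power of 22 wards by total loss.** Losses shrink the wards, which also lowers the design effect. The 10% for unequal sizes enters as a divisor of 1.1.
- Effective n per arm = 11 × m / [1 + (m − 1) × 0.05] / 1.1
- Power = Φ(0.4 × √(effective n / 2) − 1.96)

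| Total loss | Nurses left | m | Design effect | Effective n per arm | Power (normal) | Power (t, 20 df) |
|---|---|---|---|---|---|---|
| 20% (plan, T1) | 264 | 12 | 1.55 | 77.4 | 70.2% | 65.8% |
| 25% (assumed, T2) | 247.5 | 11.25 | 1.51 | 74.4 | 68.4% | 64.1% |
| 30% (assumed, T2) | 231 | 10.5 | 1.475 | 71.2 | 66.5% | 62.2% |
| 40% (assumed, T2) | 198 | 9 | 1.40 | 64.3 | 62.1% | 57.9% |

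**4. Splitting the shortfall.** At 30% loss, power is 80 − 66.5 = 13.5 points short. Of these, 80 − 70.2 = 9.8 are already missing at T1, and 70.2 − 66.5 = 3.7 come from loss after T1. At 40% loss, the part after T1 is 70.2 − 62.1 = 8.1 points.

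**The case against.** Several points on the other side are sound.

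- **No 80% claim is made for T2.** Power is stated once, and the attrition phrase itself points to T1. A reader might infer that the plan promises 80% at 9 months, but it does not. The defect is that no time point is named.
- **Loss at T2 is unknown.** A reader might take the 20% as a rate per 3 months and compound it: 0.8³ = 51% retained, m = 7.68, and power 57%. The document gives one loss between two occasions, not a recurring rate, so this figure should not carry the point.
- **80% could survive some further loss if 8 per arm were right.** If the variance is rescaled so that 8 per arm has 80% power and losses shrink the wards, 22 wards give 83.5% at 20% loss, 80.3% at 30% and 76.2% at 40%. By the plan's own scaling of the sample by 1 − loss, the figures are 80.0% at 20%, 77.4% at 25%, 74.6% at 30% and 67.9% at 40%.
- **An unstated input could justify 8 per arm.** A baseline correlation of about 0.53, an ICC of about 0.016 or a d of about 0.47 would do so. Pair-matching may also reduce variance. The section uses none of these.
- **The analysis differs from the check.** The mixed model keeps T0 and T1 data from nurses who leave later, so a completers-only formula is somewhat pessimistic at T2. More than 22 wards and the periodic prompts to complete questionnaires would also help, but no ward number or retention figure is attached to them.

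These points limit the size of the T2 effect. None supplies an attrition allowance beyond T1, and none makes 80% follow from the stated inputs.

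**Conclusion.** The point holds in a limited form. The attrition allowance ends at T1 while the nurse primary outcome runs to T2, and the power statement does not say which it describes. On the stated inputs, 22 wards give about 70% at T1 (66% with the t-test) and about 68%, 67% or 62% at T2 for an assumed total loss of 25%, 30% or 40%.

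It would be wrong to infer that 80% is secure at T1 and that attrition alone breaks it later. Most of the shortfall at 25% to 30% loss, and more than half at 40%, is present at T1 because 8 wards per arm does not follow from the inputs. The missing allowance adds 2 to 8 points.

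These figures rest on a cross-sectional comparison of two means with no baseline adjustment, the stated ICC at both time points, the same d at T1 and T2, losses spread evenly over wards, and exactly 22 wards.

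**What to change.** In Sample size calculation:

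1. Name the time point to which the power refers.
2. Replace 80% with the power that 22 wards give at T1, about 70% on the stated inputs. If 8 per arm rests on an input that is not reported, such as a baseline correlation, state it and show that it yields 8.
3. Add an explicit assumption for nurse attrition to 9 months, from the sponsor's own turnover data or as a range, with the resulting T2 power. Say that a null T2 result will be read from its confidence interval and not as proof of no lasting effect.

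The cost is a rewritten paragraph and less favourable figures. Restating the power needs no extra enrolment. Keeping 80% would: on the stated inputs with shrinking wards, it takes 28 wards at 20% loss and 30, 32 or 34 at 25%, 30% or 40%. If the sponsor wants 80%, its aim of more than 22 wards should become a number.

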### Economic evaluation

Data with regard to the economic evaluation of the SELF-program will be gathered from geriatric clients. Similar to the effect-evaluation, data will be collected through digitalized questionnaires client-data will be provided by the first responsible caregiver. Client-data will be gathered at the same time points as for the effect-evaluation in geriatric clients see Table 1. The economic evaluation is conducted according to the Dutch guidelines for economic evaluations in healthcare, taking into account a societal perspective [45]. Both a cost-effectiveness analysis (CEA) and cost-utility analysis (CUA) will be performed in which clinical outcomes and healthcare use and costs are assessed. In the CEA and CUA, incremental costs are compared with the incremental effects of the comparable treatments addressed in the trial (SELF-program versus care as usual) [45].

**Table 1 Tab1:** Overview of data collection for effect and economic evaluation

**Outcomes**	**Measures**	**Time Points**		
**Effect evaluation**		Baseline (T0)	Follow-up 1 (T1)	Follow-up 2 (T2)
*Nursing care professionals*				
Level of stimulation behavior	MAINtAIN; (19 items)	X	3 months	9 months
*Geriatric clients*				
Self-reliance in daily functioning	GARS-4; (18 items)	X	3 months	6 months
**Economic evaluation**				
Clinical outcomes				
Self-reliance in daily functioning	GARS-4; (18 items)	X	3 months	6 months
Health-related quality of life	Euro-QOL-5D (5 items)	X	3 months	6 months
Health care use and costs				
Health care utilization	Questions derived from the iMTA Medical Consumption Questionnaire	X	3 months	6 months

### Clinical outcomes

The primary outcome for the CEA will be the degree of self-reliance in daily functioning of geriatric clients, as measured by the GARS-4 [43]. Within the CUA, the health outcome of interest is given by quality adjusted life years (QALYs), which are determined by using a generic health-related quality of life measurement instrument known as the EuroQol-5D-5L (EQ-5D-5L) [46]. The instrument, of which a Dutch tariff has been derived [47], assesses five dimensions of health-related quality of life: mobility, self-care, usual activities, pain/discomfort and anxiety/depression. Each dimension is rated on a 5-point scale ranging from ‘no problems’ to ‘extreme problems’. Ratings on the five dimensions are summed and utilities of the CUA are operationalized by QALYs [45]. Last, current health status is assessed by the Dutch version of the EuroQol visual analogue scale (EQ-VAS) [47].

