#### Economic evaluation

The economic evaluation will evaluate the cost-effectiveness of the SELF-program compared with care as usual over 6 months. The principal analysis will be the incremental cost per quality adjusted life year gained from the societal perspective using the EQ-5D-5L to calculate QALYs as recommended by the Dutch Healthcare Institute [45]. This will be calculated as the mean cost difference between the SELF-program and care as usual divided by the mean QALY difference to give the incremental cost-effectiveness ratio (ICER). Use of QALYs as a generic health outcome measure allows policymakers to compare cost-effectiveness results across different sectors to guide resource allocation decisions. Unit costs will be taken from the Dutch Manual for Costing in Economic Evaluations [49] and other standard published sources. The cost of the SELF-program will also include the costs related to the external actor, who is hired to guide the role-play session.

Estimates for mean total costs and QALYs’ incremental between the SELF-program compared with care as usual over 6 months will be derived using regression analysis to control for differences in baseline utilities and costs, as well as relevant stratification variables. A secondary analysis will include the cost per point change in the primary outcome measure (GARS-4) gained of the SELF-program compared with care as usual over 6 months. Where necessary, analyses will take into account clustering at the nursing home care level via random intercept models. Regression analysis will also be used in the secondary cost-effectiveness analysis to control for potential imbalances in baseline GARS-4 values and stratification variables. To quantify uncertainty around cost-effectiveness results, non-parametric bootstrap methods will be used and 95% bias-corrected and accelerated bootstrap confidence intervals will be calculated for the mean total cost and QALY/GARS-4 incremental estimates. The bootstrap replications will also be used to construct cost-effectiveness planes and cost-effectiveness acceptability curves, from which the probability that SELF-program is cost-effective compared to care as usual at 6 months of the trial will be computed for a range of values of the willingness to pay thresholds based on current recommendations [45].

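### The EQ-5D-5L scoring sentence states a wrong rule (ratings are summed, utilities come from QALYs) and conflicts with the tariff, guideline and baseline utilities that the plan relies on elsewhere

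*Protocol article*

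**What the plan says.** The Clinical outcomes section describes the EQ-5D-5L as an instrument that "assesses five dimensions of health-related quality of life: mobility, self-care, usual activities, pain/discomfort and anxiety/depression". On the response format it says: "Each dimension is rated on a 5-point scale ranging from ‘no problems’ to ‘extreme problems". On scoring it says: "Ratings on the five dimensions are summed and utilities of the CUA are operationalized by QALYs". The same section mentions a value set ("The instrument, of which a Dutch tariff has been derived [47") but does not say that it will be applied.

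The Economic evaluation section under Data analyses makes cost per QALY over 6 months the principal economic analysis, "using the EQ-5D-5L to calculate QALYs as recommended by the Dutch Healthcare Institute". It adjusts for baseline utilities and builds acceptability curves over willingness-to-pay thresholds. The Economic evaluation section under Data collection also commits to the Dutch guidelines.

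The secondary economic analysis is the "cost per point change in the primary outcome measure (GARS-4) gained". On the GARS-4, the Geriatric clients section under Data collection says: "Only the 11 items of the ADL-subscale will be assessed". Table 1 lists "GARS-4; (18 items)" once under the effect evaluation and once under the economic evaluation.

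**The concern.** A utility for a cost-utility analysis comes from mapping the five-dimension health state to a value set, on a scale where 1 is full health and 0 is dead. An unweighted sum of ratings is not on that scale. With levels coded in the order in which they are listed, it also rises as health gets worse. The second half of the sentence reverses the construction, because utilities are the input to QALYs.

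This is not a detail left to a fuller document. A rule is stated, it is wrong, and it disagrees with the rest of the economic plan. An analyst who follows the one explicit instruction would carry a quantity on the wrong scale and with the wrong sign into the cost-per-QALY ratio, where no willingness-to-pay threshold could be applied to it.

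**Working it through.** The plan gives no utility, QALY or ICER figure, so there is none to reproduce. The check asks what the stated rule would produce if the sum were used as the utility.

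**Inputs**
- Five dimensions with five levels each (Clinical outcomes).
- Assessments at baseline, 3 and 6 months (Table 1), and a 6-month horizon (Economic evaluation, Data analyses).
- Level codes are not given. Coding 1 to 5 is assumed, with 0 to 4 as the alternative.

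**Range of the sum**
- Coded 1 to 5: 5 × 1 = 5 (best) to 5 × 5 = 25 (worst).
- Coded 0 to 4: 0 to 20. Higher is worse under both codings.
- There are 5^5 = 3,125 health states, and they collapse to 21 distinct sums. States that a tariff could value differently would share one score.

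**Area under the curve over 6 months**

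With values a, b and d at 0, 0.25 and 0.5 years:

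A = 0.25(a + b)/2 + 0.25(b + d)/2 = 0.125a + 0.25b + 0.125d

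| Case | A |
|---|---|
| Utility 1 throughout (true maximum) | 0.5 |
| Sum 5 throughout (best health) | 2.5 |
| Sum 25 throughout (worst health) | 12.5 |
| Coded 0 to 4, best and worst | 0 and 10 |
| Improving client, sums 15, 13, 11 | 1.875 + 3.25 + 1.375 = 6.5 |
| Worsening client, sums 15, 17, 19 | 1.875 + 4.25 + 2.375 = 8.5 |

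The worsening client would be credited with more QALYs than the improving one.

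**Weight of a single one-level change under the same formula**
- Present at all three assessments: 0.125 + 0.25 + 0.125 = 0.5.
- Present at 3 and 6 months: 0.25 + 0.125 = 0.375.
- Present at 6 months only: 0.125.

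**Would rescaling rescue the sum?** The transformation 1 − (S − 5)/20 restores the direction: the improving client gets 0.3 and the worsening client 0.2. It still weights every dimension and level equally and sets the worst state to 0 by construction. The plan describes no such step.

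**GARS-4 item count.** If items are scored 1 to 4 (assumed), 11 items give a range of 11 to 44 and 18 items give 18 to 72. A cost per point would differ between the two scales. The Geriatric clients section settles which applies, since the 7 instrumental items are not assessed. Table 1 is therefore the place to correct.

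**The case against.** The strongest defence is that the scoring sentence has two clauses and never says that the sum is the utility. The surrounding text points to tariff utilities: the Dutch tariff is cited, the Dutch guideline is invoked in both economic evaluation sections, baseline utilities are a regression adjustment, and the thresholds only make sense on a QALY scale. The authors may simply have meant that the five ratings are combined into a health state. This stands. A reader might infer that the planned QALYs and ICER do rest on a sum score and will be meaningless. The documents do not support that; they support a wrong sentence that contradicts the rest of the plan.

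Three further limits also stand.
- A reader might take every one-level change to be worth 0.5 of a QALY under the literal rule. That needs the change to be present from baseline onward. A change that appears only after baseline counts for less, as shown in the working.
- A reader might infer that the GARS-4 analysis counts deterioration as benefit, because the response scale runs from full independence to needing help. The article gives no item codes and never says that a higher score is better. The wording leaves the direction open; it does not state a wrong one.
- Table 1 may be giving full instrument lengths, as it does for the 19-item MAINtAIN, of which 8 items form the primary outcome. For the GARS-4 this does not fully excuse the entry, because the other items are not administered at all. It is still only a table correction.

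The defence does not remove the central error. No sentence says that the tariff is applied, and the one explicit scoring instruction is incorrect.

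**Conclusion.** The point holds as a wrong and internally inconsistent scoring rule, of moderate severity. The error itself is certain: summing ratings does not give a utility, and utilities are not derived from QALYs. The numerical damage (2.5 to 12.5 against a maximum of 0.5, with the direction reversed) is conditional on using the sum literally as the utility and on 1-to-5 coding. Under 0-to-4 coding the range would be 0 to 10, with the same reversal. Values under the tariff cannot be computed here, because its coefficients are not in the article.

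The effect is confined to the economic evaluation, where it touches the principal analysis. The MAINtAIN primary outcome, the sample size and the effect analysis are not affected. The 18-versus-11 item discrepancy for the GARS-4 is real but minor.

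**What to change.** Replace the scoring sentence with wording such as: *Each EQ-5D-5L health state is converted to a utility with the cited Dutch tariff, and QALYs are the area under the utility curve over T0, 3 and 6 months.* Delete the summed score, or keep it for description only.

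Two smaller edits: in Table 1, change both GARS-4 entries from 18 items to the 11 ADL items, and state in the cost-effectiveness analysis that the effect is improvement on the GARS ADL subscale.

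The cost is wording only. The five EQ-5D-5L items are collected in any case, so the tariff can be applied without new data, visits or budget. The wording should be settled before the economic data are analysed.
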